### Implementation and evaluation of application in the live environment (clinical trial)

#### Study design and setting

At this stage, an interventional study will be conducted through patient blinding by an assessor physician and analyst to evaluate the effects of the application on patient self-care. The designed application will be installed on patients’ smartphones and the necessary training to use it will be given to the patients and their caregivers. This application will support Android 5 and above. The study population will include patients referring to one of the general hospitals in Kashan where sampling can be done in a convenient way. Patients with hemiplegia or hemiparesis caused by a recent stroke will be chosen for this purpose. Either the patient or his/her patient caregiver must have an Android-based smartphone and be able to work with it. At least 72 h must have passed since the stroke (The acute phase of the disease must have passed) and patients must have adequate consciousness and hearing and be willing to participate in the study. Exclusion criteria will include:Patients who have some levels of consciousness disorderPatients with cognitive disorders such as dementia or memory impairmentPatients with global aphasia

The formula “n = [(Z_1−α/2_ + Z_1−β_)^2^ * (σ_1_^2^ + σ_2_^2^)]/($$\overline{x }$$_1 _− $$\overline{x }$$_2_)^2^” with the reliability of 95% and the test power of 90% based on the mean and standard deviation of baseline NIHSS obtained in the same study [29] (Z_1−α/2_ = 1.96, Z_1−β_ = 1.282, σ_1_, σ_2_ = 8, $$\overline{x }$$_1_ = 5, $$\overline{x }$$_2_ = 12) was calculated as 27 patients, which increased to 30 patients according to the available facilities which, with a 10% sample dropout, will increase to 33 individuals. Accordingly, two groups each including 33 patients (intervention and control) with stroke (66 patients in total) who meet the inclusion criteria will be selected.

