#### Data collection

The required data will be collected using valid and reliable questionnaires that are introduced as follows. Data will be collected in three stages: prior to intervention (before the intervention and at the time of discharge), two months after the intervention and three months after the intervention (in the doctor's office or in the hospital outpatient clinic). Data from National Institute of Health Stroke Scale (NIHSS) and Barthel Index (BI) questionnaires and stroke complication checklist will be filled out by the attending neurologist and other questionnaires will be filled out by patients as self-report. Completion of questionnaires by patients will be done electronically and sent online through the application. Therefore, this survey will be considered as a “closed survey” since only registered users with a valid account can access the questionnaires and submit them. Application features will be inactive until patients, complete questionnaire items. After completion, application features will be activated and the questionnaire will be deactivated to prevent response duplications. The questionnaires will be reactivated two months and three months later. In order to ensure that no data will be missing, all fields and questions will be defined as mandatory in electronic questionnaires and patients will be warned to answer all questions before sending the questionnaire.

All online questionnaires will exactly be designed the same as paper questionnaires in terms of appearance, content and sequence of questions. That is, all the questions will be placed consecutively and not on separate pages. Therefore, it can be said that the validity and reliability reported for the paper version of questionnaire will also apply to the electronic version.

It is expected that the use of this application can improve the measured variables in the intervention group compared to the control group. Specifically, the research hypotheses are that patients in the intervention group have significant differences with those in the control group in terms of indicators of physical activity, depression, quality of life, medication adherence, satisfaction with treatment, and the number of complications.

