#### Data analysis

Data analysis will be performed using IBM SPSS 22 [43]. The data will be entered anonymously using codes and numbers, which can be decoded only by one of the researchers (except the assessor or the analyst). The data will be stored in this software application and supported by a backup on another system kept in another place. The data will be first presented in the form of descriptive statistics and frequency distribution tables. The normality of the data will be checked using the Kolmogorov–Smirnov test. Depending on the type of data distribution, the mean or median of the data will be used as a criterion. In case of normal distribution of data, the mean will be used and in case of abnormal distribution (non-parametric), the median will be used for statistical calculations. In order to determine the relationship between the scores of patients’ activities of daily living, quality of life, depression, medication adherence and patient satisfaction with patients’ group type (control or intervention), an independent t-test will be used. If there is a significant difference between the intervention group and the control group, the effect of the intervention will be specified. Repeated measures analysis of variance (ANOVA) will also be used to analyze multivariate and control the effects of confounding variables on dependent variables. Confounding variables will include: patient age, sex and educational level, which can affect the final results. In all tests, a significance level of 0.05 will be considered. Pearson or Spearman correlation coefficient (according to the type of variable distribution) will be used to determine the relationship between the usage duration of the program and the score of the measured variables. After categorizing the time of application usage, one-way ANOVA or Kruskal–Wallis’s test (depending on the type of variable distribution) will be used to determine the relationship between the measured variables and the time of application usage. Chi-square test will be used to determine the relationship between the type of complications in both groups. Also, to determine the relationship between the scores of the measured variables before and after the intervention, a paired t-test will be used in each group separately. Hypothesis H0 will indicate the absence of correlation and Hypothesis H1 will indicate the existence of correlation between the measured variables.

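### The named t-test and repeated measures ANOVA, combined with excluding patients after re-stroke or withdrawal, can bias the arm comparison if outcome-related loss differs by arm

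*Protocol article*

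**What the plan says.** All references are to the protocol article.

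- **Study design and setting** allows for loss only through the sample size: "with a 10% sample dropout, will increase to 33 individuals" per arm, 66 in total. The calculation is on NIHSS, with "σ_1_, σ_2_ = 8".
- **Data collection** sets three measurement times: baseline, two months and three months. The attending neurologist completes NIHSS, the Barthel Index and the complication checklist, with follow-up in the doctor's office "or in the hospital outpatient clinic". Patients send the other questionnaires through the app. Mandatory fields are meant to prevent missing data.
- **Intervention** counts re-stroke as a complication in both arms, yet takes a patient with re-stroke during the intervention out of the study and substitutes a new patient.
- **Discussion** (limitations paragraph) says that patients who become unwilling are excluded at whatever point this happens.
- **Data analysis** names SPSS 22 and an independent t-test between arms for daily living, quality of life, depression, adherence and satisfaction. It then says: "Repeated measures analysis of variance (ANOVA) will also be used to analyze multivariate and control the effects of confounding variables on dependent variables". The covariates are age, sex and education. NIHSS is not in the t-test list, so the repeated measures ANOVA is the only named between-arm comparison of scores that could cover it.

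The article states no analysis set and no rule for missing visits.

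**The concern.** The plan expects losses and describes two ways in which randomised patients leave. One of these, re-stroke, is itself an outcome event. The methods it names are not neutral to such losses. An independent t-test compares whoever has a score. Repeated measures ANOVA in its conventional form (a property of the method, not a statement in the article) keeps only patients with all three visits, so a missed three-month visit also removes an observed two-month score.

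Mandatory fields deal with unanswered items, not missed visits. The reminders in the Discussion concern the questionnaires, not the neurologist's NIHSS and Barthel ratings.

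Losses could plausibly differ by arm. Only the intervention arm is asked to use the app for one hour on five days a week, and the Intervention section itself cites excessive sample loss as a reason not to go beyond eight weeks. If the patients who leave differ in outcome from those who stay, and differently by arm, part of any observed difference would reflect who remained.

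**Working it through.** **1. The plan's own sample size.** Inputs from Study design and setting: "Z_1−α/2_ = 1.96", z for power 1.282, SD 8 in both arms, means 5 and 12.

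n = (1.96 + 1.282)² × (64 + 64) / 7² = 10.51 × 128 / 49 = 27.46 per arm. The plan states 27 (28 if rounded up). It is then raised to 30, and 30 × 1.10 = 33. Dividing instead, 30 / 0.9 = 33.3. The plan's figures reproduce within rounding.

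**2. Does the 10% allowance protect power?** 33 × 0.9 = 29.7 per arm, giving power of about 91–92% for a 7-point difference. If 10% were missing independently at each of the two follow-up visits (an assumption; the plan gives a single 10%), the share with all three visits is 0.9² = 0.81. That is 33 × 0.81 = 26.7 per arm, with power about 88–90%. Power is therefore not the problem.

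**3. Size of the possible bias.** The documents give no loss rates by arm and no link between loss and outcome, so these are assumptions: 33 per arm, no true effect, SD 8 at each visit, visit correlations 0.6–0.8, and month-3 loss depending on the month-2 NIHSS (logistic, slope 1 to 2 per SD). Completers are compared at month 3 with a two-sided t-test at 0.05.

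| Loss, arm 1 v arm 2 | Mean false difference (NIHSS points) | Type I error |
|---|---|---|
| 20% v 0% | 1.1–1.7 | 0.08–0.13 |
| 15% v 5% | 0.6–0.8 (0.5 under the weakest selection) | 0.06–0.07 |
| 12% v 8% | 0.2–0.4 | 0.045–0.058 |
| 10% v 10%, same mechanism | about 0 | about 0.05 |

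The standard error is about 2.0 throughout; by formula, 8 × √(2/30) = 2.07. Against the planned difference of 7 points, 0.6–0.8 is 9–11% and 1.1–1.7 is 16–24%.

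The figures sit at the upper end of the correlation range. Because loss depends only on the month-2 score, the month-3 bias is proportional to the correlation between those two visits. At 0.6 instead of 0.8 it is three-quarters as large: about 0.8–1.3 points at 20% v 0%, and 0.45–0.6 at 15% v 5%.

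**4. A bound with equal rates but different reasons.** Suppose one arm loses exactly its worst 10% and the other loses 10% at random. The mean of the first arm shifts by φ(1.2816)/0.9 = 0.1755/0.9 = 0.195 SD, or 0.195 × 8 = 1.56 points. Simulated with 3 of 33 lost per arm, type I error is 0.049 if loss in that arm is unrelated to outcome, 0.063 at a correlation of 0.5 and 0.12 at a correlation of 1. Equal rates cancel only if the reasons are also alike.

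**5. What a likelihood-based analysis would do.** In the setting of step 3 with about 10% overall loss, all in one arm, completers show a bias of 1.50 points (standard error 2.05). An analysis that uses the observed baseline and month-2 scores shows 0.03 (standard error 2.06). It removes the bias in this setting and gains no precision.

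**The case against.** **The article is silent on missing data; it does not prescribe a complete-case analysis.** This stands. The statistical analysis plan is not shown, so the absence of an imputation or sensitivity plan is not the criticism. But the article does fix the tests and the exclusions, and those can be judged as written.

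**A reader might infer that patients will be lost through death or disability and that the result will therefore be biased.** The documents do not support this. No cause is attached to the 10%. The losses described are re-stroke and unwillingness, and the point rests on those.

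**A reader might also infer that inability to travel would remove all outcomes.** It would not. EQ-5D-3L and the other self-reported scales are sent through the app, with reminders and phone calls, and a caregiver may help. Attendance matters for NIHSS, Barthel and the complication checklist.

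**The plan applies 10% to each arm, and equal loss by the same mechanism gives no bias.** Correct. A bias of 1.5 points needs about 20% loss in one arm and none in the other, or equal rates with quite different reasons. The larger figures are worst cases.

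**A mixed model brings no gain in precision, and the simulation favours it.** Both are true. Loss there depends on an observed score, which is where such a model is valid. It would not fully correct loss driven by an unrecorded deterioration, and it cannot supply scores that stop being collected after a re-stroke exclusion. Changing the test without dealing with the exclusion would be only half a remedy.

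**Conclusion.** The point holds in a limited form. The named t-test and repeated measures ANOVA, combined with the removal of randomised patients after re-stroke or withdrawal, leave the arm comparison open to bias that the 10% allowance does not address. The bias is possible, not demonstrated. Its size depends on assumed loss patterns: negligible when loss is equal and alike in both arms, a fraction of a point at moderate imbalance, and well under one standard error even in the worst case. The amounts in NIHSS points also scale with the SD of 8, which the plan takes from baseline NIHSS in another study. Power is adequate on the plan's figures if 66 are randomised. The change is worth making because a better method is available in the software already named, at almost no cost.

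**What to change.** 1. In Data analysis, replace the repeated measures ANOVA and the t-tests for the arm comparison with a linear mixed model for repeated measures (SPSS MIXED). Include arm, visit, arm-by-visit and the stated covariates (age, sex, education). Name NIHSS among the outcomes. Use every available score from all randomised patients, in the arm to which they were randomised.
2. Reconcile the Intervention section with this. It counts re-stroke as an outcome while removing the patient from the study. For the analysis, re-stroke patients stay in the set with all their collected scores, and any replacement counts as an additional patient. The article should say which scores are collected after a re-stroke, since the model cannot recover those that are not. This concerns the analysis set only, not the patient's treatment.
3. Treat patients excluded for unwillingness in the same way: keep what was collected before they left.
4. Report losses, with reasons, and deaths by arm. A rank-based sensitivity analysis placing deaths at the worst rank is optional.

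Also reconcile the total: Study design and setting gives 66, but the Abstract and the Randomization section give 60, so the dropout allowance does not reach the allocation list. With 60 randomised and 10% lost, 27 per arm remain and power is 89.5% (88.4% by the t distribution).

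The cost is rewording two sections and slightly more analysis work. No new instrument or software is needed.

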**Discussion:**

The assessed outcomes will include stroke severity using National Institute of Health Stroke Scale (NIHSS) score, ability to perform activities of daily living using Barthel Index (BI) score, depression rate using Beck Depression Inventory (BDI-II) score, quality of life using EQ-5D-3L score, medication adherence using Modified Morisky Medication Adherence Scale (MMAS-8) score, patient satisfaction using Patient Satisfaction Questionnaire (PSQ) score and the number and type of complications in patients in two groups. These outcomes will be assessed at baseline, after two months and after three months from the beginning of the intervention. Intervention effects on the measured variables will also be evaluated using appropriate statistical tests based on the type of variable distribution. Potential consequences of the study might be the improvement of the measured variables in the intervention group compared to that of the control group. The expected results are that the intervention may significantly improve the status of the measured variables in the intervention group compared to that of the control group. If the outcomes of the intervention group do not change significantly compared to those of the control group, it can be due to different reasons. However, this can most likely be attributed to incorrect or insufficient use of the application by patients.

*Trial registration*: This protocol is registered in the Iranian registration of clinical trial (IRCT) on November 7, 2020 with the code IRCT20201015049037N1. URL: https://irct.ir/trial/51674

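### NIHSS sizes the trial but is in none of the named between-group tests, and no primary outcome or visit is set while every test runs at 0.05

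*Protocol article*

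**What the plan says.** Under Study design and setting, the sample size is "based on the mean and standard deviation of baseline NIHSS obtained in the same study", at two-sided 0.05 and 90% power, with means of 5 and 12 and a standard deviation of 8 in each group. It gives 27 per group, raised to 30 for practical reasons and to 33 for dropout. The abstract lists NIHSS first among seven outcomes.

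Under Data analysis, the independent t-test between groups is assigned to "activities of daily living, quality of life, depression, medication adherence and patient satisfaction with" group. Complications are compared by a chi-square test. The t-test sentence is followed by: "If there is a significant difference between the intervention group and the control group, the effect of the intervention will be specified". A repeated measures ANOVA is added to handle age, sex and education, but the outcomes it applies to are not listed. The error rule is "In all tests, a significance level of 0.05 will be considered".

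Outcomes are measured at baseline and at two follow-up visits. The abstract times these visits "after two months and after three months from the beginning of the intervention"; Data collection times them "two months after the intervention and three months after the intervention". Nowhere is one outcome or one visit called primary, and the hypotheses at the end of Data collection list several outcomes side by side.

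**The concern.** A power calculation is meaningful for one designated comparison. Here the calculation is for NIHSS, but of the abstract's seven outcomes NIHSS is the only one with no named between-group test. The article does more than condense: it spells out a list, and the sizing outcome is not on it.

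At the same time, the comparisons that are named have no ranking, and each is run at the full 0.05. If the app does nothing, the chance that at least one of them reaches significance is well above 5%, and nothing in the article says which result carries the trial's conclusion. A reader of the final report could not tell a confirmatory result from one picked out among several.

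This cannot be put down to detail reserved for an analysis plan. The primary outcome and its time point are core protocol content, and the Background section says the article was written with the SPIRIT checklist.

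**Working it through.** **1. The plan's own sample size.** Inputs from Study design and setting: z = 1.96 and 1.282, SD = 8 in both groups, means 5 and 12.

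n = (1.96 + 1.282)² × (8² + 8²) / (5 − 12)² = 10.5106 × 128 / 49 = 27.46 per group.

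The stated 27 is reproduced (rounding up would give 28). The calculation is for NIHSS and no other outcome.

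**2. Which outcomes have a named group comparison.**

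| Outcome (abstract) | Named between-group test (Data analysis) |
|---|---|
| NIHSS | none |
| Barthel Index | t-test |
| BDI-II | t-test |
| EQ-5D-3L | t-test |
| MMAS-8 | t-test |
| PSQ | t-test |
| Complications | chi-square |

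That makes six named comparisons, counting complications as one test.

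**3. Chance of at least one false positive, each test at 0.05.** If k tests are independent, it is 1 − 0.95^k.

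- One visit, k = 6: 1 − 0.95⁶ = 1 − 0.735 = 26.5%.
- Both follow-up visits, k = 12: 1 − 0.95¹² = 1 − 0.540 = 46.0%. This assumes that each comparison is repeated at each visit, which the article does not say.

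The outcomes will be correlated, and the article gives no correlations. The range below assumes normal test statistics with one common correlation r, simulated with 400,000 draws per cell and counted as positive when any |Z| > 1.96.

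| Tests | r = 0 (formula) | r = 0.3 | r = 0.5 | r = 0.7 |
|---|---|---|---|---|
| 6 (one visit) | 26.5% | 24.1% | 20.7% | 16.5% |
| 12 (both visits, assumed) | 46.0% | 39.7% | 32.0% | 23.2% |

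The within-group paired tests, the usage-duration tests and any separate tests of the 19 checklist complications are not counted.

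**4. Does naming NIHSS as primary need more patients?** On the plan's own inputs, power = Φ(7 / (8 × √(2/n)) − z).

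- One primary test at two-sided 0.05 (z = 1.96): n = 27 gives 0.895; n = 30 gives 7/2.066 − 1.96 = 1.43, so 0.923; n = 33 gives 0.945.
- All seven outcomes co-equal at one visit with Bonferroni (0.05/7 = 0.0071): n = 30 gives 0.758, and 90% power would need 42 per group.

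A single primary outcome fits the planned size; seven co-equal ones do not.

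**5. Visit wording.** The abstract counts from the start of the intervention. The audit paragraph in the main Discussion counts from patient registration. Data collection also says that the questionnaires reopen two and three months later, following the baseline completion that unlocks the app. These point to an anchor at the start. The remaining phrase in Data collection, read literally, counts from after an 8-week intervention and would move both visits by about two months.

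**The case against.** The strongest reply is that the repeated measures ANOVA may cover NIHSS, since NIHSS is a declared outcome and the ANOVA is applied to dependent variables in general. It could also assess the group effect across visits without one test per visit. This stands in part. NIHSS cannot be said to go entirely unanalysed, and doubling the test count for two visits has to be labelled an assumption. But the ANOVA's outcomes are not named, it is introduced as an addition for confounder control, and the sentence that draws the conclusion follows the t-test list.

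A reader might infer that the app will be declared effective if any one outcome is significant. The article does not say so. Its conclusion sentence follows a list of separate scores and can be read score by score, as an effect on that score. The percentages are therefore the chance of at least one false-positive comparison, not of a formal claim that the app works.

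A reader might also count seven outcomes at two visits, giving 1 − 0.95¹⁴ = 51.2%. That includes NIHSS among the tests although NIHSS is not in the named list, and it assumes repetition at both visits. It does not describe the plan as written.

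Finally, the visit wording might look like a serious contradiction. It is a real inconsistency but a minor one, because most of the text agrees on a start-of-study anchor.

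**Conclusion.** The point holds. The outcome that sizes the trial has no named between-group comparison, no outcome or visit is primary, and all tests are at 0.05 without adjustment. For the six named comparisons at one visit, the chance of at least one false positive is about 16% to 27%, against a nominal 5%. If each is repeated at both visits, it is about 23% to 46%. The upper ends assume independence; the lower ends assume an equal correlation of 0.7, a figure that is not in the article. The range depends on these assumptions and on the test count, but even its lowest value is more than three times the nominal level. The absence of a primary outcome and visit, and of NIHSS from the test list, depends on no assumption. The registry record was not available, so the conclusion concerns the article only.

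**What to change.** Add NIHSS to the between-group comparison in Data analysis. Name one primary outcome at one visit, tested at two-sided 0.05. Total NIHSS is the choice consistent with the sample size calculation. The two-month visit, at the end of the 8-week intervention, is a natural option, but the article does not rank the visits and the sponsor should choose.

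Label all other outcomes and the other visit as secondary, and either adjust them for multiplicity (Holm, for example) or report them with confidence intervals and no confirmatory claim. State which outcomes the repeated measures ANOVA covers. Enter the change in the trial registry before analysis; Trial status already provides for protocol changes to be recorded there.

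As a minor correction, reconcile the visit timing in Data collection with the abstract and with the audit paragraph of the main Discussion, so that one anchor is used throughout.

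The cost is wording and a registry update. On the plan's own inputs no extra patients are needed (step 4 of the working). The real price is that secondary outcomes become harder to claim.

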#### Intervention

Intervention for patients in the intervention group (in addition to usual care) will include an Android-based application that has all the functional requirements approved by the experts in the analysis and software design phases. This application will contain audio, video, textual files and games to improve lower and upper limb function and activities of daily living, prevent and reduce depression, reduce and manage pain and other possible complications of stroke, medication reminders and whatever playing a role in improving patient outcomes, and will be designed according to experts' opinion. Patients will be advised to use the application 5 days a week and for a period of 1 h each day. The duration of the intervention will be 8 weeks (40 sessions in total). A systematic review study [21] showed that the duration of intervention to improve physical activities using mobile phones was between 4 and 6 weeks, which could be extended to 10 weeks for greater effectiveness. According to the conditions in the country and the opinion of experts and follow-up protocols of patients, intervention for more than 8 weeks was not recommended due to the possibility of excessive sample fall. Patients will access the application by creating valid accounts. Account creation by patients and physicians will be done by the system admin and demographic information will be recorded for them; however, the usernames defined for users cannot be changed by them. The application can record the number of times and hours of application use by the user. In order to learn how to use the application, users can contact one of the research team members. A member of the research team will also make weekly phone calls to make sure patients know how to use the application. Intervention for patients in the control group will include usual medical care based on the opinion of the responsible neurologist (This can include physiotherapy or occupational therapy). An application will be installed on the smartphones of these individuals which lacks the main capabilities of the application and only contains electronic questionnaires. Installation of this application will be done only for blinding purposes. Intervention duration and the time of measuring the outcomes will be the same for both groups. Figure 2 shows the flowchart of protocol for interventional trial. Re-stroke will be recorded in both groups and finally it will be considered as one of the complications of stroke in both groups. Nevertheless, an individual with re-stroke during the intervention due to entering the acute phase of the disease will be excluded from the study and replaced by another individual. To replace the new individual, the researcher will return to the hospital and replace another person who meets the study inclusion criteria (In case of excessive sample fall). The research hypothesis is that using the proposed intervention along with usual care can improve stroke outcomes. Therefore, this study can be considered as a superiority trial. Routine rehabilitation interventions (such as electrotherapy) cannot be eliminated at this time. Therefore, no hypothesis can be defined for this intervention alone.

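### The planned usage–outcome tests make no adjustment for baseline, so they may show a confounded association of unknown direction even if app use has no effect

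*Protocol article*

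**What the plan says.** The Data analysis section of the protocol article relates usage to outcome in two ways. The first is a Pearson or Spearman correlation, chosen by distribution, whose stated purpose is "to determine the relationship between the usage duration of the program and the score of the measured variables". The second puts the same question to a one-way ANOVA or Kruskal–Wallis test, which the section introduces with the words "After categorizing the time of application usage". No covariate is named for either.

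The same section does name covariates: "Confounding variables will include: patient age, sex and educational level". These belong to the repeated measures ANOVA, and the list contains neither baseline NIHSS nor the baseline value of the outcome. The error rate is common to everything: "In all tests, a significance level of 0.05 will be considered".

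The exposure comes from the app's own log. The Intervention section says: "The application can record the number of times and hours of application use by the user". That section recommends one hour a day, five days a week, for eight weeks, but the time actually spent is up to the patient.

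On a null trial result, the Discussion paragraph of the abstract allows for several reasons, then adds that "this can most likely be attributed to incorrect or insufficient use of the application by patients".

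**The concern.** Usage time is not randomised. The participants have hemiplegia or hemiparesis, and the app contains exercises and games for the limbs, so disability, mood and adherence at baseline could all influence how much it is used. Those characteristics are also the outcomes (NIHSS, Barthel Index, BDI-II, MMAS-8), so their baseline values are likely to predict their follow-up values. A common cause of usage and follow-up score produces a correlation between the two without any effect of usage.

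What is at stake is interpretation. The abstract already leans towards insufficient use as the reason for a null result. If heavy users had better scores only because they started better, the planned tests would seem to bear that reading out when the app had done nothing. If heavy users started worse, the same tests would suggest that the app does harm.

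**Working it through.** **Inputs from the article.** The plan gives no figure for the usage analysis, so there is none to reproduce. The group size comes from the sample-size paragraph in Study design and setting: (1.96 + 1.282)² × (8² + 8²) / (12 − 5)² = 10.51 × 128 / 49 = 27.46. The article states 27, raises it to 30 and, with 10% dropout, to 33. About 30 evaluable app-arm patients is therefore the relevant n. The significance level is 0.05; two-sided testing is taken here.

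**Assumptions, not in the article.** r₁ is the correlation of baseline severity with usage, taken from −0.5 to +0.3. r₂ is the correlation of baseline with follow-up score, taken from 0.5 to 0.9. Higher scores mean worse status. Usage has no effect: given baseline, usage and follow-up are independent. The categorised analysis is represented by tertiles.

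**Step 1: the induced correlation.** Under these conditions corr(usage, follow-up) = r₁ × r₂. For r₁ = −0.3 and r₂ = 0.7 this is −0.21.

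**Step 2: a hand check of the false-positive rate.** By Fisher's z with n = 30, atanh(0.21) × √27 = 0.2132 × 5.196 = 1.108. The chance of passing 1.96 is P(Z > 1.96 − 1.108) + P(Z > 1.96 + 1.108) = 0.197 + 0.001, or about 20%.

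**Step 3: simulation, 20,000 null trials per setting, n = 30.** Entries are the percentage significant at 0.05.

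| r₁ | r₂ | r₁ × r₂ | Raw correlation | Tertile ANOVA | Either test | Adjusted for baseline |
|---|---|---|---|---|---|---|
| 0 | 0.7 | 0 | 5.0 | 4.9 | 8.1 | 5.2 |
| −0.2 | 0.5 | −0.10 | 8.2 | 6.6 | 11.5 | 5.0 |
| −0.2 | 0.9 | −0.18 | 15.8 | 10.4 | 19.6 | 4.9 |
| −0.3 | 0.5 | −0.15 | 12.4 | 8.9 | 16.1 | 5.1 |
| −0.3 | 0.7 | −0.21 | 20.2 | 12.6 | 23.9 | 5.1 |
| −0.3 | 0.9 | −0.27 | 31.0 | 19.0 | 35.0 | 5.0 |
| −0.5 | 0.5 | −0.25 | 26.9 | 16.3 | 30.7 | 4.8 |
| −0.5 | 0.9 | −0.45 | 72.5 | 48.5 | 74.5 | 5.1 |
| +0.3 | 0.7 | +0.21 | 20.0 | 12.6 | 23.7 | 4.8 |

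The hand check agrees with the simulation (20% against 20.2%). With n = 33 the unadjusted rates under confounding are mostly slightly higher (22.3% at −0.3 and 0.7), and the adjusted rates over all settings are 4.7–5.3%. The first row also shows that testing usage both as continuous and as categories gives about 8% with no confounding at all.

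**Step 4: would a change score do?** With equal variances, corr(usage, follow-up − baseline) = −r₁ × √((1 − r₂)/2). For r₁ = −0.3 and r₂ = 0.7 this is 0.3 × √0.15 = +0.116. The simulation gives a mean of +0.114, with 9.2% of trials significant. The bias changes sign but does not go away.

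**The case against.** The strongest objection concerns direction. A reader might infer that the analysis will show a false dose-response because less disabled patients can use the app more. The article does not say so, and some of it points the other way. Eligibility requires only that the patient or a caregiver can work the phone, the Discussion brings in a caregiver where the patient cannot, and a team member telephones weekly. More disabled patients might log as much time, or more. This stands: size and sign are unknown, a zero usage–severity correlation removes the problem, and a positive one reverses it. Even with confounding, the false result is non-significant more often than significant in most of the settings examined. What the objection does not do is make the unadjusted tests safe, because a caregiver who steps in on account of disability still ties usage to disability.

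Two further inferences are tempting. One is that controls will be pooled into the usage analysis; the other is that the cut-points will be chosen after looking at the data. The article states neither. It is silent on both, a condensed article may leave such details to an analysis plan, and usage of the program reads most naturally as usage of the app arm's program. Nor does the article say that the usage correlation will be used to test its explanation of a null result. The abstract only leans towards that explanation, after allowing for others.

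It is also fair that the article speaks of scores without saying whether follow-up or change scores are meant. Step 4 of the working shows that a simple change score would not rescue the analysis. Finally, the return to 5% after adjustment follows from a model in which baseline is the only confounder, so adjustment should not be oversold.

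**Conclusion.** The concern holds in a limited form. The article names unadjusted tests for a self-selected, post-randomisation exposure, and the confounders it lists are attached to another analysis and omit baseline severity. That is a choice of method, not a detail left out.

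Followed as written, the plan may produce an association that is not causal. At n = 30 the false-positive rate of the raw correlation runs from nominal, when usage is unrelated to baseline severity, up to 73% at the extreme of the assumed range (r₁ = −0.5, r₂ = 0.9). The usage–severity and baseline–follow-up correlations are assumptions; the document supplies neither. Adjustment is nominal only in a model where baseline is the sole confounder, so motivation, mood and caregiver support could still bias the result.

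The randomised between-group comparison, which carries the trial's hypotheses, is untouched. This should be changed, but it does not threaten the main result.

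**What to change.** Replace the two planned tests with one analysis in the app arm: a regression or partial correlation of each follow-up score on usage as a continuous variable, adjusted for the baseline value of the same score and for baseline NIHSS. Do not substitute a simple change score. If the categorised ANOVA or Kruskal–Wallis test is kept, fix its categories in advance and treat it as descriptive.

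State that the usage analysis is exploratory and non-causal because residual confounding, for example by motivation or caregiver support, remains. State also that it will not be used to explain a null between-arm result.

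The cost is changed analysis wording and one or two degrees of freedom per model (one when NIHSS is itself the outcome, two otherwise). Baseline scores and usage logs are already to be collected, so no new data are needed.
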